## Abstract

**Introduction:**

Vitrectomy combined with internal limiting membrane (ILM) peeling, flap or tamponade is widely used in the treatment of macular diseases, such as macular hole (MH) and high myopia macular hole retinal detachment (HMMHRD). However, movement of the ILM to a suitable position to prevent displacement is a difficult operation. Improving visual function after surgery remains controversial. Compared with ILM, the thicker and more flexible lens capsule is easy to obtain and operate. Previous studies have confirmed the effectiveness of lens capsule flap in the treatment of MH. This study aims to evaluate the efficacy and safety of vitrectomy combined with lens capsule flap transplantation in the treatment of HMMHRD.

**Methods and analysis:**

This single-centre, single-blind, prospective, randomised clinical trial will include 54 patients with HMMHRD who will first undergo phacoemulsification and intraocular lens implantation and then vitrectomy combined with lens capsule flap transplantation (experimental group) or ILM tamponade (control group). Study participants will be randomly allocated in a 1:1 ratio to experimental and control groups. Follow-up will be conducted 1, 3 and 7 days and 1, 3 and 6 months after surgery in both groups. Necessary examinations will be performed at each follow-up visit. Measurement outcomes include postoperative situation of macular hole closure, best-corrected visual acuity, macular retinal function and macular retinal sensitivity. The primary outcome is type I closure rate of MH 6 months after operation. Intergroup comparisons of the proportions of patients with type I closure of MH will be performed with Fisher’s exact test.

**Ethics and dissemination:**

Full ethics approval for this study was obtained from the Ethics Committee of Shanghai General Hospital, Shanghai Jiaotong University, Shanghai, China. The outcomes of the trial will be disseminated through peer-reviewed journals and at scientific conferences.

**Trial registration number:**

ChiCTR2200057836.

Strengths and limitations of this studyThis is the first randomised controlled trial investigating the efficacy and safety of vitrectomy combined with lens capsule flap transplantation in the treatment of high myopia macular hole retinal detachment.In addition to anatomical measurement, functional measurements, including best-corrected visual acuity, macular retinal function and macular retinal sensitivity, are also used to evaluate the postoperative efficacy.Based on whether the macular hole reaches 400 µm, this trial will adopt the stratified randomisation method through the central random system.Strict quality control measures, including adequate concealment of randomised group allocations, will be implemented.Difference in preoperative lens opacity affecting the baseline visual acuity of the two groups and difficult evaluation of vitreoretinal surgery are the limitations of this trial.

## Introduction

High myopia is a common cause of vision loss. Globally, about 163 million individuals (2.7% of the world population) suffered from high myopia in 2000. With the increasing prevalence of HM, an estimated 1 billion individuals (9.8% of the world population) will suffer from high myopia in 2050.^1^ Patients with high myopia have a higher risk of ocular disorders, such as cataract and glaucoma, than those without high myopia. In the field of the fundus, high myopia is associated with a series of pathological complications, including posterior staphyloma, myopic macular schisis (MMS), preretinal membrane, chorioretinal dystrophy, macular hole (MH) and retinal detachment (RD).^2–4^ In patients with high myopia, about 6% of patients will develop MH, which is about 10 times higher than in individuals without high myopia.^5^ Patients with high myopia have a long ocular axis and a high risk of posterior scleral staphyloma. Continuous traction of the vitreous leads to the formation of MHs. The liquid in the vitreous reaches beneath the retinal neuroepithelial layer through the macular holes to form subretinal fluid (SRF), which will lead to high myopia macular hole retinal detachment (HMMHRD).^6^ HMMHRD can be clearly diagnosed by optical coherence tomography (OCT). Once it occurs, vision deteriorates drastically, reducing quality of life. It is one of the serious complications threatening the vision of patients with high myopia.^7 8^ Possible mechanisms of HMMHRD include vitreoretinal traction caused by epiretinal membrane, residual vitreous cortex, inner limiting membrane (ILM) and retinal vascular system,^9^ which makes the vertical and tangential traction generated by the epiretinal membrane and ILM^10 11^ and further weakens the adhesion between retinal neuroepithelial layer and retinal pigment epithelium (RPE). The long axis reduces the extension of the retina, resulting in the relative shortening of the retina and subsequent retinal splitting and detachment.^12^

The key to the treatment of HMMHRD is to restore the normal anatomical structure of the macular region, improve the continuous traction state of the vitreous to the retina and induce retinal reattachment. The main surgical procedures include extrascleral surgery (scleral buckling, macular banding and posterior scleral reinforcement), intraocular surgery (vitrectomy) and combined intraocular and extraocular surgery. Currently, vitreoretinal surgery is the mainstream surgical method for the treatment of HMMHRD. Among them, pars plana vitrectomy (PPV) can relieve the mechanical traction of the vitreous cortex on the macula, restore the anatomical structure, effectively reduce retinal oedema and facilitate fluid exchange, and promote the recovery of retinal function in the macular region. It is one of the most routinely performed operations.^13^ However, the abnormalities of the anatomical structure in high myopia, such as long ocular axis, retinal choroidal atrophy at the posterior pole, posterior scleral staphyloma and ‘macular white hole’, lead to increased surgical difficulty, resulting in low retinal reduction and hole closure rate and high recurrence rate in patients with HMMHRD after simple vitrectomy. In addition, scar healing, retinal interlayer structure disorder, RPE atrophy and ganglion cell damage occur in MHs after operation, which lead to unsatisfactory visual function recovery, even if retinal anatomical reduction was achieved.^14 15^ Therefore, to improve the success rate of surgery and preserve the visual function of patients as much as possible, combined macular interface surgery is needed after vitrectomy removes the traction of the vitreous to the macula. The combination of surgical methods, such as ILM peeling, ILM flap and ILM tamponade, are currently in practice. Improving the visual function of patients based on improving the reduction rate is the key to the selection of macular interface surgery for HMMHRD.^16 17^

Although these operations can improve the healing rate of MH, obtaining the ILM tissue at the edge in patients with high myopia remains challenging. The challenge is due to the problems of posterior scleral staphyloma, retinal choroidal atrophy and difficulty in identifying the ILM.^18 19^ Moreover, because the ILM is originally soft, under the influence of the long axis of high myopia, ILM softens further under traction. Therefore, moving the ILM to a suitable position to prevent displacement is difficult.^19 20^ As a result, the role of improving visual function postsurgery remains controversial. Therefore, the choice of operation mode of macular interface is particularly important.

In 2019, Grewal *et al*^21^ first reported that the lens capsule was transplanted to the MH for the treatment of refractory MH. Peng *et al*^22 23^ used an autologous or allogeneic lens capsule to treat refractory MH. The healing rate can reach 90% and 96%, and the visual acuity of patients can be improved. Similar to the ILM, the lens capsule is a kind of basement membrane. Although the lens capsule is thicker than the ILM, it is quite flexible. Therefore, positioning the lens capsule at a designated place in the retina is easier than the ILM. For most patients who need surgery for HMMHRD, the degree of lens turbidity reaches the surgical indication of cataract phacoemulsification. Therefore, most doctors will choose to complete the operation together with cataract surgery to easily obtain the capsule tissue. The mechanism of lens capsule transplantation in the treatment of MH is similar to that of ILM. The lens capsule can be used as a scaffold to promote the proliferation and migration of Müller cells in the retina and promote the healing of MHs. The study found that the lens capsule as a stent still existed and did not become thinner after nearly 3 years of follow-up.^23^ Appropriate size and reasonable placement of lens capsule graft is the key to successful surgery.^23^ Mastery of certain surgical skills is necessary to fill the lens capsule at the MH. Moreover, lens capsule transplantation cannot only promote the healing of MH but also improve the vision of patients.^20 24 25^ In addition, lens epithelial cells on the anterior capsule flap can be removed using distilled water, resulting in low antigenicity.^23^ In the actual operation of capsule transplantation, Chen *et al*^16 20^ reported that the lens capsule is easier to process and insert MH than ILM, making it possible to vigorously promote this technology.

Based on the advantages of easy access, easy operation of lens capsule, combined with the clinical prognosis of high retinal reattachment rate and better improvement of visual function found in the capsule transplantation group in the previous study, our team plans to conduct a prospective randomised controlled trial of vitrectomy combined with lens capsule flap transplantation in the treatment of HMMHRD to explore the efficacy and safety of this operation in retinal reattachment and functional recovery after the treatment of HMMHRD.

## Methods and analysis

### Overview

This is a single-blind, prospective and randomised clinical trial (RCT) being conducted at Shanghai General Hospital affiliated with Shanghai Jiaotong University. The patients have a clear diagnosis of HMMHRD and require vitrectomy. Our hypothesis is that vitrectomy combined with lens capsule flap transplantation in the treatment of HMMHRD can achieve a higher proportion of retinal reattachment and better functional recovery. After comprehensive ophthalmic and physical examinations, the patients will be randomised into an experimental group and control group to receive treatment.

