### Objective

The study aims to evaluate the efficacy and safety of vitrectomy combined with lens capsule flap transplantation in retinal reattachment and functional recovery in patients with HMMHRD.

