#### Anatomical measurement

OCT will be used to assess the retina and macula before and after surgery. According to the postoperative situation of retinal reattachment and MH closure, the surgical result will be classified as: (1) type I closure: the two ends of the MH are closely connected and close to the RPE layer without any obvious exposure of the RPE layer and subretinal fluid (SRF); (2) type II closure: the two ends of the MH are not connected, and the edge of the hole is closely attached to the RPE layer with a distance between the two ends. The exposed RPE layer can be observed without any obvious SRF; (3) unclosed: the two ends of the MH are not connected, and the edge of the hole is still raised and tilted away from the RPE layer. The SRF can be observed further.^27 28^

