### Primary outcome

The primary outcome is type I closure rate of MH 6 months after operation.

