### Secondary outcomes

The following indicators will be used to comprehensively assess anatomical outcome: (1) type I closure rate of MH 3 months after operation; (2) type II closure rate of MH 6 months after operation; and (3) type II closure rate of MH 3 months after operation.

Functional outcomes will be assessed as follows: (1) changes in BCVA 3 and 6 months after operation compared with baseline; (2) changes in P1 wave response density in the macular region 3 and 6 months after operation compared with baseline; and (3) changes in macular retinal sensitivity 3 and 6 months after operation compared with baseline.

Furthermore, the number of adverse events and reactions, abnormality of ophthalmic examination, abnormal systemic symptoms and laboratory results will be recorded at each follow-up visit.

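### Retinal reattachment is the stated hypothesis but no listed outcome compares it between arms, and the type II closure rates listed instead have no fixed direction when tested alone

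*Protocol article*

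**What the plan says.** - **Hypothesis** (Overview): the capsule flap operation "can achieve a higher proportion of retinal reattachment and better functional recovery". This statement is directional.
- **Objective**: to evaluate efficacy and safety "in retinal reattachment and functional recovery in patients with HMMHRD". It names reattachment but gives no direction.
- **Primary outcome**: "The primary outcome is type I closure rate of MH 6 months after operation".
- **Secondary anatomical outcomes**: type I closure at 3 months and, as items 2 and 3, "2) type II closure rate of MH 6 months after operation; and (3) type II closure rate of MH 3 months after operation". The functional secondaries are changes in visual acuity, P1 response density and retinal sensitivity.
- **Abstract**: "Measurement outcomes include postoperative situation of macular hole closure, best-corrected visual acuity, macular retinal function and macular retinal sensitivity". Reattachment is not in this list either.
- **Grading** (Anatomical measurement): three OCT grades, based jointly on reattachment and hole closure. Type I has joined hole edges and no obvious subretinal fluid (SRF). In type II the edges lie on the retinal pigment epithelium (RPE) but apart: "The exposed RPE layer can be observed without any obvious SRF". Unclosed has raised edges, and SRF is still seen.
- **Statistical analysis**: categorical variables are given as numbers and frequencies and compared by Fisher's exact test.

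**The concern.** The functional half of the hypothesis has matching outcomes, but the anatomical half has none. An article may leave much to a full protocol or analysis plan. This one, however, sets out its primary and secondary outcomes, and that list does not match its own hypothesis.

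Two things are at stake. First, a positive result on type I closure could be reported as confirming better reattachment when the arms reattach equally. Any reattachment comparison made later would be a post hoc choice. Second, two of the three anatomical secondary outcomes are type II rates. Type II is the middle of three exclusive grades, so a significant difference in it does not by itself say which arm did better.

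**Working it through.** **1. What the plan's sample size is for.** Inputs from Sample size: type I closure 96% v 65%, two-sided 5%, power 0.80.
- The arcsine formula is n = 2(1.960 + 0.842)² / h², with h = 2(arcsin√0.96 − arcsin√0.65) = 0.863. It gives n = 21.06, against the stated 21 per group.
- With 20% attrition, 21/0.80 = 26.25, rounded up to 27 per group, 54 in total.

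The stated figures are reproduced. They concern type I closure only. The article gives no rate for type II, unclosed or reattached eyes.

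**2. Reattachment in terms of the grades.** Types I and II have no obvious SRF and unclosed has SRF. If every eye falls in one of the three grades, then

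reattached = type I + type II = 1 − unclosed.

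**3. How far type I fixes reattachment.** Hold type I at 96% v 65%, a difference of 31 points. Type II can then be 0% to 4% in the capsule arm and 0% to 35% in the control arm.
- Largest reattachment difference: (96 + 4) − (65 + 0) = +35 points.
- Smallest: (96 + 0) − (65 + 35) = −4 points.

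**4. The same in counts.** Take 27 evaluable eyes per arm and the whole numbers nearest the planning rates: type I in 26/27 (96.3%) v 18/27 (66.7%), two-sided Fisher p = 0.011. Let the remaining capsule eye be type II, so that capsule reattachment is 27/27. Vary the unclosed eyes among the other 9 control eyes (assumed, for want of a figure in the article):

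| Control unclosed | Control type II | Type II, capsule v control | Type II p | Reattached, capsule v control | Reattachment p |
|---|---|---|---|---|---|
| 0 | 9 | 1/27 v 9/27 | 0.011 | 27/27 v 27/27 | 1.0 |
| 2 | 7 | 1/27 v 7/27 | 0.0504 | 27/27 v 25/27 | 0.49 |
| 5 | 4 | 1/27 v 4/27 | 0.35 | 27/27 v 22/27 | 0.051 |
| 6 | 3 | 1/27 v 3/27 | 0.61 | 27/27 v 21/27 | 0.023 |
| 9 | 0 | 1/27 v 0/27 | 1.0 | 27/27 v 18/27 | 0.0018 |

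The primary result is the same in every row. Reattachment goes from no difference to a clear one, and is below 0.05 once 6 or more control eyes are unclosed. In these rows the type II p-value moves the opposite way: it is smallest where reattachment is equal.

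**5. Direction of a type II difference.**
- *Lower is good*: the first row. The capsule arm has fewer type II eyes (1/27 v 9/27, p = 0.011) because more reached type I, and all eyes in both arms are reattached.
- *Lower is bad*: let both arms have 18/27 type I. One arm has 1 type II and 8 unclosed, the other 8 type II and 1 unclosed. Type II is 1/27 v 8/27, p = 0.024, and the arm with fewer type II eyes has the worse reattachment, 19/27 v 26/27.

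Both are significant and both show fewer type II eyes in one arm, yet they mean opposite things.

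**The case against.** The best defence is that nothing is lost. Type I closure requires the absence of obvious SRF, so reattachment is part of the primary outcome. Type I and type II rates are both listed at 3 and 6 months, so a reader can add them and recover reattachment at each visit. Read beside type I, a type II rate is no longer ambiguous: 26 + 1 v 18 + 9 shows at once that every eye is closed. Reporting all three grades is also routine detail that an article may leave out.

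Most of this stands, and it limits the point. A reader might infer that type I closure says nothing about reattachment, that the type II p-values are uninterpretable, or that the hypothesis cannot be tested from the trial's data. The documents support none of these. Type I is stricter than reattachment, not unrelated to it. Type II is ambiguous only when taken alone. The OCT data needed are planned at every visit. Nor does the Objective claim a higher reattachment rate; only the Overview does. The case with all eyes reattached is one end of an assumed range and not a forecast, and it uses 27 evaluable eyes per arm although 20% attrition is planned.

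The defence does not supply a named comparison. The article never lists the sum of types I and II, or the unclosed rate, as an outcome, while its analysis section applies Fisher's test to categorical variables and the type II rate is one of the outcomes listed.

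**Conclusion.** The point holds as a mismatch between the hypothesis and the named outcomes, not as a gap in measurement. The listed outcomes contain no comparison of reattachment, and type I closure does not determine it. With the planning type I rates fixed, the reattachment difference can lie anywhere from +35 to −4 percentage points. In the count example its p-value runs from 1.0 to 0.002 beside the same primary p of 0.011. A positive primary may or may not support the hypothesis as worded.

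This rests on two assumptions: that the three grades cover every eye, and that the type II split is unknown, as the article leaves it. The validity of type I closure as the primary outcome is not in question. The change should be made, and is easiest now, because Trial status describes the study as still preparatory.

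**What to change.** 1. In Secondary outcomes, replace the two stand-alone type II rates with one derived outcome at the same visits: retinal reattachment (overall closure), defined as type I or type II, with no obvious SRF on OCT, at 3 and 6 months. One outcome is enough; under the article's grading, reattachment and overall closure are the same variable, and listing both would duplicate a test.
2. Report the number of type I, type II and unclosed eyes by arm at each of these visits, so that type II is always seen in context.
3. Reword the hypothesis in the Overview so that type I closure at 6 months is the primary claim and reattachment and functional recovery are secondary. Bring the Objective into line.

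The cost is a wording change to the protocol and registry entry before the first patient is enrolled; Trial design already provides for telling the registry of modifications. The primary outcome and sample size stay as they are, and no examination is added, since Table 1 already schedules OCT and B-ultrasound at every visit.

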### Objective

The study aims to evaluate the efficacy and safety of vitrectomy combined with lens capsule flap transplantation in retinal reattachment and functional recovery in patients with HMMHRD.

### Trial design

The prospective, single-centre RCT will enrol 54 participants that will be randomised in a 1:1 ratio to the experimental group (vitrectomy combined with lens capsule flap transplantation) or control group (vitrectomy combined with ILM tamponade). The patient’s ophthalmic and systemic medical history and first examination results at admission will be recorded during the screening visit for the trial. Vitrectomy combined with lens capsule flap transplantation or ILM tamponade will be performed by one experienced surgeon. The protocol (date: 24 June 2022, version: 1.1) was developed and updated in accordance with the Consolidated Standards of Reporting Trials guidelines. This protocol was written in accordance with the Standard Protocol Items: Recommendations for Interventional Trials guidelines^26^ and was approved by the Institutional Review Board of Shanghai General Hospital (online supplemental file 1), approved ID: 2022SQ284.1). The trial has been registered with the Chinese Clinical Trial Registry (ChiCTR; http://www.chictr.org.cn/, No. ChiCTR2200057836). Any protocol modifications will be communicated to the participants and trial registry. Trial results will be disseminated on trial registration (ChiCTR) or through a publication. Participants have the right to withdraw their consent and discontinue participation at any time. A flow chart of the trial design is shown in figure 1.

10.1136/bmjopen-2022-064299.supp1Supplementary data

**Figure 1 F1:**
[figure not shown]
Flow chart of the trial design. ILM, inner limiting membrane.

### Recruitment

Participants will be recruited by the surgeon during hospitalisation without any other form of advertisement. Interested patients will be invited to discuss the benefits and potential risks related to the vitrectomy combined with lens capsule flap transplantation. Participants meeting all the inclusion criteria will be fully informed of their responsibilities and all procedures involved in the trial. They will be asked to sign the written informed consent before enrolment. The English translation of informed consent can be seen in online supplemental file 2.

10.1136/bmjopen-2022-064299.supp2Supplementary data

#### Inclusion criteria

The inclusion criteria are as follows: (1) patients ≥50 years old who were diagnosed as HMMHRD by indirect ophthalmoscopy, macular OCT, fundus photography and B-ultrasound examination; (2) equivalent spherical dioptre ≤–6.00 D or axis length ≥26 mm; (3) MH as main cause of RD; (4) turbid lens without obvious calcification in the lens capsule, requiring combination with cataract surgery; (5) the range of RD within the retinal vascular arch of the posterior pole; and (6) consent to undergo surgical treatment and regular follow-up and sign relevant informed consent.

